## Abstract

**Methods::**

We will enroll 100 participants with opioid use disorders receiving methadone maintenance treatment at an addiction treatment center and randomly allocate them to an experimental or control group. The experimental group will receive 12 sessions of light needle therapy within 4 weeks, while the control group will receive sham light needle treatment without any laser output. Urinary morphine levels were assessed before and after treatment. Participants will be asked to self-report their number of episodes or days of heroin use and heroin craving/refusal to use heroin in the previous week before and after treatment on a visual analogue scale score of 0 to 10. Quality of life will be reported using the Short Form-12v2 before and after 4 weeks of treatment. Pulse diagnosis and heart rate variability will be evaluated before and after treatment. Baseline patient characteristics will be compared between the groups using the independent *t* test and the *χ*^2^ test. Data between the 2 groups will be compared using generalized estimation equations, and paired *t* tests.

**Objective::**

This study aims to investigate the effect of adjuvant light needle therapy in patients with opioid use disorder on methadone maintenance treatment.


Acupuncture based on the principles of the traditional Chinese meridian theory is performed by inserting fine, sterile needles into acupuncture points to achieve “Qi and blood,” or a “yin and yang” state of harmony.^[15]^ Acupuncture therapy is inexpensive and simple, has fewer side effects than other treatments used for opiate addiction, and is safe for both pregnant and parturient women.^[16,17]^ The application of acupuncture to opiate addiction was 1^st^ reported by [name] in Hong Kong in 1972, who reported that electroacupuncture at 4 body acupoints and 2 ear acupoints could alleviate opioid withdrawal symptoms in patients with opiate addiction.^[18]^ A breakthrough protocol was developed in 1985 by Dr M. Smith, the head of the US National Acupuncture Detoxification Association (NADA). The NADA protocol reported that the insertion of 5 needles into bilateral ear acupoints at the sympathetic, shenmen, kidney, lung, and liver points could relieve withdrawal symptoms, prevent drug cravings, and increase patient compliance in long-term therapeutic programs.^[19]^ In 1996, the WHO accepted acupuncture as a treatment for drug abuse.^[20]^ This method of healing has been reported to normalize hyperreactivity or hypoactivity of the mesolimbic dopamine system, activate analgesic effects via both the μ and κ receptors, prevent relapse of drug-seeking behavior by regulating neurotransmitters, and alleviate illicit drug withdrawal syndrome, including physical and psychological symptoms.^[21–24]^

Light needle or laser acupuncture (also termed low-level laser therapy), the use of nonthermal, low-intensity laser beams that penetrate tissues and stimulate acupoints, has recently become more popular among acupuncture practitioners owing to its noninvasive, safer, pain-free, time-saving properties, lower manual skill requirement, and fewer adverse effects than traditional acupuncture.^[25]^ A study showed that light needles achieve neural responses similar to those of needle acupuncture.^[26]^ These features make light needles a more acceptable and effective option for patients on an abstinence plan. A previous study suggested that laser intervention was beneficial for opioid addicts to address drug cravings and improve their quality of life.^[27]^ This study aims to investigate whether light needle treatment combined with methadone maintenance treatment (MMT) is effective in the management of OUD.

## 2. Methods

### 2.1. Ethics approval

The trial was approved by the Chang Gung Medical Foundation Institutional Review Board (IRB no. 202200041A3). The protocol was registered with ClinicalTrials.gov (identifier NCT05341219) and Chinese Clinical Trial Registry (identifier ChiCTR2200059497). Written informed consent will be obtained from each participant. Personal information about the potential and enrolled participants will be collected, shared, and maintained in a separate closet to protect confidentiality before, during, and after the trial.

### 2.2. Study design

This randomized controlled trial is being conducted in the Department of Psychiatry and Chinese Medicine at Kaohsiung Chang Gung Memorial Hospital. The study was initiated in March 2022 and will continue until February 2024. Patients enrolled from our institution’s addiction treatment center are being randomly allocated to the experimental group (light needle plus methadone maintenance treatment, n = 50, expected) or the control group (light needle without laser output plus methadone maintenance treatment, n = 50, expected). The study participants will receive 12 sessions of light needle therapy within 4 weeks. The study design is illustrated in Figure 1.

**Figure 1. F1:**
[figure not shown]
Flowchart showing movement of patients through the study.

### 2.3. Participants

The diagnosis of OUD will be confirmed using the diagnostic criteria of the Diagnostic and Statistical Manual of Mental Disorders, 5^th^ Edition. We will recruit patients aged 20 to 70 years with OUD who have received methadone maintenance treatment for at least 1 month and have provided informed consent. A psychiatrist will assess the eligibility of each potential participant before recruitment. Patients with critical illness, those who have taken Chinese medicine or received acupuncture within 30 days, those who are considered unsuitable for recruitment by a physician, and those who are not willing to provide informed consent will be excluded.

### 2.4. Sample size and randomization

We calculated a sample size of 98 in accordance with a 2-way repeated-measures analysis of variance with a medium effect size of 0.25, pre- and post-measurements for each of the 2 groups, a significance level (*α*) of 0.05, and a desired power (1–*β*) of 0.80.^[28]^ Expecting a 2% dropout rate, 100 participants will be recruited. A random permutation block of block size 4 is selected using a research randomizer that generated a random sequence.^[29]^ Allocation concealment was performed by using numbered containers. The researchers recruited and assessed participants in sequentially numbered, opaque, sealed, and stapled envelopes. Trial participants, outcome assessors, and data analysts will be blinded after assignment to interventions labeled A and B for both groups.

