### 2.7. Statistical analysis

Data will be displayed as mean ± standard deviation. Baseline participant characteristics between the experimental and control groups will be assessed and compared using independent *t* tests and chi-square tests. The differences between the 2 groups will be compared using an independent *t* test. Paired *t* test will be used to compare the 2 groups. All analyses will be performed using the Statistical Package for the Social Sciences (SPSS) for Windows version 22 (Statistics 22, IBM Corp., Armonk, NY). Statistical significance is set at P < .05.

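### The 98 participants and 80% power come from a repeated-measures ANOVA that is not the planned analysis, and the figure appears to rest on a group main effect that dilutes the treatment effect

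*Protocol article*

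**What the plan says.** Section 2.4 of the protocol article sizes the trial as follows: "We calculated a sample size of 98 in accordance with a 2-way repeated-measures analysis of variance with a medium effect size of 0.25". The other inputs are "pre- and post-measurements for each of the 2 groups", "a significance level (*α*) of 0.05" and "a desired power (1–*β*) of 0.80". It then adds: "Expecting a 2% dropout rate, 100 participants will be recruited". Section 2.2 expects 50 participants in each arm.

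The section does not say whether the group effect, the time effect or their interaction is powered. It gives no correlation between the two measurements, and it does not translate the 0.25 into a difference between arms at week 4.

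The analysis is described in two places. Section 2.7 says: "The differences between the 2 groups will be compared using an independent *t* test". It does not say whether this test is applied to week-4 values or to changes from baseline. The methods paragraph of the abstract names generalised estimating equations and paired t tests for the comparison of the arms. Neither place names a repeated-measures ANOVA.

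**The concern.** A sample size justification should give the power of the test that will decide the trial, for an effect the reader can recognise. Here the sizing model appears nowhere in the analysis, and the two descriptions of the analysis disagree with each other.

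The sizing model also has a problem of its own. With pre and post values in two groups, a repeated-measures ANOVA offers several effects, and the required number depends strongly on which one is chosen and on the correlation. Under randomisation the treatment effect is the difference at week 4 or, equivalently in expectation, the group-by-time interaction. The group main effect is something else: it averages the week-4 difference with a baseline difference that is expected to be zero.

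At stake is how a null result on urinary morphine or self-reported heroin use would be read. The 80% invites the reader to treat it as evidence against a medium effect. Whether the trial can bear that reading depends on assumptions that section 2.4 does not give.

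**Working it through.** **Inputs.** From section 2.4: f = 0.25, 2 groups, m = 2 measurements, alpha 0.05, power 0.80, N = 98, dropout 2%. From section 2.2: equal allocation, so 49 per arm at N = 98. The correlation rho is not given, so it is varied here. The SD is taken as equal at both visits and in both arms, and tests are two-sided.

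**1. Reproducing 98.** For the group main effect the noncentrality is lambda = f² × N × m / (1 + (m − 1) × rho), with 1 and N − 2 degrees of freedom.
- N = 98, rho = 0.5: lambda = 0.0625 × 98 × 2 / 1.5 = 8.17, power 80.8%.
- N = 96, rho = 0.5: lambda = 8.00, power 79.9%.

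So 98 is the smallest even number that reaches 80%. Other correlations give 66 (rho 0), 84 (0.3), 104 (0.6) and 110 (0.7). The dropout step also reproduces: 98 / (1 − 0.02) = 100.

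**2. The interaction does not give 98.** Here lambda = f² × N × m / (1 − rho).
- rho = 0: N = 66.
- rho = 0.3: N = 46.
- rho = 0.5: N = 34.

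The number falls as rho rises, so 66 is the maximum for non-negative rho. Other variants also miss: lambda = f² × N gives 128, lambda = f² × (N − 2) gives 130, and a one-sided t test gives 102.

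**3. What f = 0.25 means for the group main effect.** With two equal groups, f = 0.25 is a difference of 2 × 0.25 = 0.5 SD in the quantity tested, here the average of pre and post. With a baseline difference of zero, the average difference is half the week-4 difference, so the week-4 difference must be 2 × 0.5 = 1.0 SD.

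Conversely, a week-4 difference of 0.5 SD leaves an average difference of 0.25 SD, or f = 0.125. Then lambda = 0.015625 × 98 × 2 / 1.5 = 2.04, and the power is 29.3% at rho = 0.5.

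**4. Power of the candidate analyses for a week-4 difference of 0.5 SD.** For a t test with n per arm, the noncentrality is d / √(2/n).
- Week-4 values, n = 49: 0.5 / √(2/49) = 2.475, power 68.8%. With n = 50 it is 69.7%. Power of 80% needs 64 per arm (128 in total) or, at 98, a difference of about 0.57 SD (79.8%).
- Change scores, or a group-by-time contrast, with d = 0.5 / √(2(1 − rho)): 54.4%, 68.8% and 88.5% at rho 0.3, 0.5 and 0.7.
- ANCOVA on baseline, approximated with d = 0.5 / √(1 − rho²): 72.9%, 80.8% and 92.9% at rho 0.3, 0.5 and 0.7.

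**5. Power if the week-4 difference is 1.0 SD.** The t test on week-4 values with 49 per arm has 99.8% power.

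**The case against.** The strongest objection is that the 69% belongs to a different effect from the one that yields 98. Section 2.4 never states 0.5 SD at week 4; it states an f inside a repeated-measures model. If that f is taken literally on the pre-post average, the week-4 difference is 1.0 SD and the t test has 99.8% power. This stands. A reader might infer that the planned t test has 69% instead of 80% power for the same effect, but the documents do not support that. The 69% applies only if *medium* is read as 0.5 SD at week 4.

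Second, the group main effect and the correlation of 0.5 were found by working back from 98, and 0.52 also gives 98. This stands too. It is a well-supported inference, since no other standard variant tried gives 98, but section 2.4 does not say it.

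Third, the between-arm analysis is not settled. The abstract's generalised estimating equations are a repeated-measures method, nearer to the sizing model than a t test, and section 2.7 leaves open which values are tested. So 69% is one value in a range, and no single figure can be called the power of the trial. That does not rescue the 98: the treatment effect in a pre-post model of that kind is normally the group-by-time term, which does not give 98 at f = 0.25.

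Finally, the same 98 gives about 81% power for 0.5 SD under ANCOVA at a correlation of 0.5. The number enrolled may therefore be adequate even though its stated justification is not.

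**Conclusion.** The point holds in this form: the 80% at 98 participants is not tied to any analysis the protocol plans. It is reproduced only by an effect that halves the treatment difference. Section 2.4 supports one of two readings, and each needs correcting. Either the trial is sized for a 1.0 SD week-4 difference that it does not disclose, or *medium* means 0.5 SD at week 4. On the second reading the group main effect has 29% power, a t test on week-4 values 69%, and a change-score test 54% to 89% for correlations of 0.3 to 0.7.

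These figures assume equal SDs, two-sided tests, 49 evaluable participants per arm and, for all but the week-4 t test, the stated correlation. The choice of effect behind the 98 is inferred. The documents do not support the stronger conclusions that the trial has 69% power, or that it needs more participants.

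**What to change.** First reconcile the abstract and section 2.7, so that both name the same primary between-arm analysis. ANCOVA of the week-4 value adjusted for baseline is preferable, because the baseline is already collected and the adjustment gains power.

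Then replace the repeated-measures basis in section 2.4 with the power of that analysis for a stated week-4 difference, giving the assumed correlation and a range. For ANCOVA:

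> With 98 evaluable participants, a two-sided 5% test of the week-4 difference adjusted for baseline has 81% power for 0.5 SD if the pre-post correlation is 0.5 (73% at 0.3, 93% at 0.7).

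If an unadjusted t test is kept, say that it is applied to week-4 values and state 69% power for 0.5 SD and about 80% for 0.57 SD. The correlation in the ANCOVA version is itself an assumption, which is why the range belongs in the text.

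The cost is a rewording of section 2.4 and the alignment of section 2.7 with the abstract. Enrolment stays at 100. The drawback is that the stated power may look less favourable than 80%.

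### A single published block size of 4 at one hospital, with recruiters and the treating physician not listed as blinded, lets anyone who learns earlier labels foresee on average one third of allocations

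*Protocol article*

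**What the plan says.** All of this stands in the protocol article.

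- **Block size (section 2.4).** "A random permutation block of block size 4 is selected using a research randomizer". One constant size is given.
- **Setting (section 2.2).** One hospital, no stratification stated, allocation described in the present tense, study period March 2022 to February 2024. The arms are "light needle plus methadone maintenance treatment, n = 50, expected" and "light needle without laser output plus methadone maintenance treatment, n = 50, expected".
- **Concealment (section 2.4).** "Allocation concealment was performed by using numbered containers", followed by "The researchers recruited and assessed participants in sequentially numbered, opaque, sealed, and stapled envelopes".
- **Blinding (section 2.4).** "Trial participants, outcome assessors, and data analysts will be blinded after assignment to interventions labeled A and B for both groups". Those who recruit and the physician who treats are not in this list.
- **Treatment (section 2.5).** The same physician applies the laser to every participant. Goggles for the physician and a shield for the participant are meant to limit what each sees.
- **Entry (section 2.3).** A psychiatrist judges eligibility before recruitment. Among those excluded are "those who are considered unsuitable for recruitment by a physician".

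**The concern.** An opaque sealed envelope hides its own content. It does not hide what can be inferred from envelopes already opened. In a block of 4 with two allocations to each arm, the last label is always fixed by the first three, and sometimes the third is fixed as well. With one site, no stratification stated and a single published size, a person who knows the order of past labels can place the block boundaries by counting.

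The A and B labels do not remove this, because past labels are enough to predict the next label. Knowing the next label becomes directional once someone knows or guesses which label is the active laser. With only two labels, identifying one arm identifies every participant.

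What would be at stake is selection at entry. If a person with influence over enrolment foresaw the next arm, the judgement-based exclusion in section 2.3 could be used differently according to that arm. Such bias cannot be reliably repaired in the analysis.

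**Working it through.** **Inputs.** Block size 4 (section 2.4); two arms of 50 expected, so 1:1 (section 2.2); 100 participants (section 2.4). The article states no predictability figure. Its own numbers fit together: 100 / 4 = 25 complete blocks, and 25 × 2 = 50 per arm. The sample size does not depend on this point.

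**Assumption.** The observer knows all earlier labels in the block. The article does not state this for anyone.

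**Certain allocations, block of 4.** The six possible sequences are equally likely.

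| Sequences | Number | Certain allocations per block |
|---|---|---|
| AABB, BBAA | 2 | 2 of 4 (50%) |
| ABAB, ABBA, BABA, BAAB | 4 | 1 of 4 (25%) |

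Average share = (2 × 2 + 4 × 1) / (6 × 4) = 8/24 = 1/3. Over 25 blocks that is 33.3 of 100 allocations on average, with a 95% range of 29 to 38 and absolute limits of 25 and 50. One third is therefore an average and not a ceiling.

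**Best guess, block of 4.** The observer guesses the arm that is behind and tosses a coin when the arms are level. The chance of being right, by position, is:

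- first: 1/2
- second: 2/3
- third: (1/3) × 1 + (2/3) × (1/2) = 2/3
- fourth: 1

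Average = (1/2 + 2/3 + 2/3 + 1) / 4 = 17/24 = 70.8%, against 50% by chance.

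**If earlier labels are unknown.** Each label is equally likely at every position, so no allocation is certain and guessing succeeds 50% of the time.

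**Alternatives, with the same knowledge of earlier labels.** Fixed blocks were enumerated exactly. Varied blocks were simulated (1,000 lists of 100 allocations), with an observer who knows the possible sizes and every past label and updates the likely block size and position after each one.

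| Scheme | Certain | Best guess right |
|---|---|---|
| Fixed 4 (plan) | 33.3% | 70.8% |
| Fixed 6 | 25.0% | 68.3% |
| Fixed 8 | 20.0% | 66.6% |
| Random 4, 6 | about 5% | about 69% |
| Random 4, 6, 8 | about 2% | about 68% |

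Varying the size removes nearly all of the certainty but little of the advantage in guessing. That advantage disappears only if past labels are kept from those who enrol.

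**The case against.** The strongest reply is that the whole calculation is conditional. The article nowhere says that recruiters learn earlier labels, and sequentially numbered, opaque, sealed envelopes are an accepted method. Directional selection also needs past labels, the identity of the active label and control over entry to come together in one person or in people who share information. The article does not join these roles: a psychiatrist judges eligibility, a traditional Chinese medicine physician treats, the physician behind the discretionary exclusion is not identified as the treating one, and the goggles may partly mask the treating physician. Who holds the list is detail that an article may leave to the full protocol. All of this stands, and it limits the point to a vulnerability. It does not remove the stated choice of a small, constant and disclosed block.

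Three stronger readings are tempting, and the article does not support them.

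- *Outcome assessors are unblinded because they handle the envelopes.* The envelope sentence is garbled, and assessed may there mean eligibility. The next sentence lists outcome assessors as blinded. An A or B label alone does not reveal the active arm.
- *Two conflicting concealment methods are described.* Numbered envelopes can be the numbered containers, so the second sentence may simply specify the first.
- *A baseline imbalance of a given size will follow.* Any figure in standard deviations needs an assumed strength of selection, which the article does not supply.

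**Conclusion.** The point holds as a conditional weakness in a stated design choice. Given knowledge of the earlier labels in a block, on average 33.3% of allocations are certain (25% to 50% in a single block) and 70.8% can be guessed. Without that knowledge none is certain. The article leaves recruiters and the treating physician off the blinded list but does not say that they learn past labels, so it shows neither that allocations were foreseen nor that enrolment was affected. The exclusion on a physician's judgement is a possible route and no more. The envelope sentence needs rewording because, as printed, it sits awkwardly beside the blinding of outcome assessors. The point is worth acting on because the change is cheap and selection at entry is hard to undo later.

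**What to change.** 1. For allocation numbers not yet used, regenerate the list with randomly varied block sizes, for example 4, 6 and 8. Withhold the sizes from everyone who enrols, treats or assesses.
2. Because best-guess success falls only to about 68%, also complete eligibility and baseline measures before an envelope is opened. Keep the list and all past labels from staff who recruit or collect outcomes.
3. Reword the envelope sentence in section 2.4 to say what the researchers did with the envelopes and which assessment is meant, so that it agrees with outcome assessors being blinded.

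If allocation has already finished, step 1 no longer applies. The sponsor should then clarify who held and opened the envelopes and whether anyone who enrolled participants knew past labels.

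**Cost.** A short amendment and a new list for the remaining numbers; no extra participants, and the separation in step 2 can use existing staff. The downside is a small possible final imbalance between arms, at most 4 if the last block is an unfinished block of 8 (four allocations made, all to one arm). This assumes that the new list starts after a completed block of 4; a switch inside a block could add up to 2.

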### 2.5. Interventions

The study participants will receive 12 sessions of light needle therapy within 4 weeks using a gallium aluminum arsenide laser (Physiolaser Olympic; maximal power, 60 mW; wavelength, 655 nm; area of probe, 0.008 cm^2^; power density, 7.5 W/cm^2^; pulsed-wave; 3305 Hz, 1168 Hz; RJ-Laser, Reimers & Janssen GmbH, Waldkirch, Germany). Similar acupuncture points will be used in both groups. Participants in the control group will receive sham light needle therapy without laser stimulation, whereas those in the experimental group will receive 135 J of energy delivered from 6 light needles placed between LU7 and LU9 (Fig. 2). Light needle therapy was applied at each point for 15 minutes. The same trained and experienced physician will perform laser application for each participant. The latter is a licensed traditional Chinese medicine physician in Taiwan with > 10 years of traditional acupuncture experience and > 5 years of laser acupuncture experience. The physician and participant will use protective goggles and a laser shield, respectively, to inhibit visual perception during the light needle treatment.

